### Methods for additional analyses

In this trial, the subgroups of pathological features will be managed based on the primary and secondary endpoints stratified by tumor size and surgical margin status.

### Interim analyses

We will perform interim analyses if the 5-year IBTR is > 5% in patients who received only low-dose tamoxifen or only underwent RT; furthermore, we will discontinue this non-inferiority trial according to the assumption that the cumulative incidence of IBTR in the experimental (tamoxifen) or control groups (RT) was 6% at 7 years.

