### Sample size

This study is designed to evaluate whether the efficacy of low-dose tamoxifen in reducing IBTR is not inferior to that of whole breast irradiation in patients with low-risk and ER-positive breast DCIS. We hypothesize that in all patients who meet the cohort 1 criteria of the ECOG E5194 study and have ER-positive status in the tumor, the 7-year IBTR rate in those who underwent BCS alone will be < 10.5% (assumption: 6–7%). In our previous study, breast DCIS patients who underwent BCS alone had the ECOG E5194 cohort 1 criteria, in whom the 7-year IBTR rate was 5% and 8% in the ER-positive and ER-negative groups, respectively [7]. For the ER-positive group tumors, most patients received tamoxifen as an adjuvant setting. Under these assumptions, we hypothesized that for low-risk breast DCIS, the 7-year IBTR rate would be approximately 6% in patients who underwent BCS alone (neither tamoxifen nor RT). The current trial was designed to evaluate whether the administration of low-dose tamoxifen (tamoxifen 5 mg for 5 years; experimental group) is not inferior in decreasing the cumulative incidence of IBTR when compared with the prescription of RT (50 Gy in 25 fractions or 40.05 Gy in 15 fractions; control group). We assume that a 6% incidence of IBTR at 7 years will be observed in participants who underwent whole breast RT alone and expect that the cumulative incidence of 7-year IBTR will not be > 6% in participants who receive low-dose tamoxifen (5 mg for 5 years).

In total, 385 patients are needed in each group to provide 90% β-power with an α type I error of 5% (margin, IBTR difference, 5%); this permits a loss of 5% of patients due to follow-up at 5 years (statistical methods are shown in Table 2). As approximately 5% of patients cannot tolerate the side effects of low-dose tamoxifen and will receive RT, we estimate that 405 patients will be enrolled in the tamoxifen arm. Therefore, 810 patients will be enrolled in this randomized non-inferiority trial. The targeted number of breast events is not described in the protocol, but the ripeness of the data from this trial will be revaluated and deliberated by Taiwanese and Japanese teams. If at least 80% of case report forms are returned 5 years after starting treatment, we will properly consolidate this trial’s corrected data.

**Table 2 Tab2:** Statistical methods

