**α: type 1 error—> 0.05**
**β: power—> 0.9**
**Assume (no-RT) low risk IBTR: 6%**
**Assume that Tamoxifen = RT = 6%**
**Assume a margin (IBTR difference: 5%)**
**N = (Z**_**α**_** + Z**_**β**_**)**^**2**^**xS**^**2**^**/Δ**^**2**^ = **385 (per arm)**
**N = 2 * n = 770 (total)**

### Recruitment

Patients will be recruited among those with breast DCIS who underwent BCS and visited the outpatient department of participating sites of the TBCC-ARO DCIS trial. In the current protocol, no advertising or inducements will be permitted and recruited. Patients will be randomized by the TBCC-developing “Clinical Study Information System” (CSIS) by logging clinicopathological information on their respective websites.

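### The only discontinuation level named, 6% IBTR at 7 years in either arm, is the rate the design assumes for both arms, and the rule ignores the tamoxifen-minus-RT difference

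*Protocol article*

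**What the plan says.** The Interim analyses section of the protocol article has two parts. The first opens a look: "We will perform interim analyses if the 5-year IBTR is > 5% in patients who received only low-dose tamoxifen or only underwent RT". The second concerns stopping: "we will discontinue this non-inferiority trial according to the assumption that the cumulative incidence of IBTR in the experimental (tamoxifen) or control groups" was 6% at 7 years. It gives no inequality, confidence limit, minimum number of patients or comparison between arms.

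The Sample size section sets the planning rates. For the control arm: "We assume that a 6% incidence of IBTR at 7 years will be observed in participants who underwent whole breast RT alone". For the experimental arm, it expects that "the cumulative incidence of 7-year IBTR will not be > 6% in participants who receive low-dose tamoxifen". Table 2 puts the two together as "Assume that Tamoxifen = RT = 6" per cent. Non-inferiority is defined on the difference ("margin, IBTR difference, 5" percentage points), and the size follows: "In total, 385 patients are needed in each group to provide 90% β-power with an α type I error of 5" per cent.

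**The concern.** A discontinuation level should separate a trial that is going wrong from one that is going to plan. Here the level equals the planned result, so chance alone puts an arm on either side of it.

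The rule also does not address the trial's question, for three reasons:

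- It looks at one arm at a time, whereas non-inferiority is a statement about tamoxifen minus RT.
- It joins the arms with *or*, so a high RT rate alone can meet it, although that is no evidence against tamoxifen.
- It counts patients by the treatment they actually had. This leaves out, for example, the roughly 5% whom the Sample size section expects to switch from tamoxifen to RT. The adherence section, in contrast, keeps patients who refuse their assigned treatment in an intention-to-treat analysis.

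At stake is a trial that is halted, or argued over, when tamoxifen is truly equal to RT or well inside the margin.

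**Working it through.** **Inputs.** From the Sample size section and Table 2: 7-year IBTR 6% in both arms, margin 5 points, α 5% (sidedness not stated), power 90%, 385 per arm, 405 per arm enrolled. From Interim analyses: more than 5% at 5 years, and 6% at 7 years. The document gives no expected 5-year IBTR. I assume constant hazard and vary it with Weibull shapes from 0.5 (front-loaded) to 1.25. Arms are independent, follow-up is complete and there is a single look.

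**1. The plan's own figure.** n = 2 × 0.06 × 0.94 × (1.645 + 1.282)² / 0.05² = 386.4, or 387 per arm with one-sided 5%. This agrees with the stated 385. One-sided 2.5% gives 475 and does not.

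**2. Implied 5-year rate.** 1 − 0.94^(5/7) = 4.32%. The trigger is therefore 5 − 4.32 = 0.68 points above plan. Conversely, 5% at 5 years corresponds to 1 − 0.95^(7/5) = 6.9% at 7 years.

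**3. Chance of a look, both arms truly on plan.** 5% of 385 is 19.25, so 20 events are needed. P(X ≥ 20 | 385, 0.0432) = 0.231 per arm. For at least one arm: 1 − (1 − 0.231)² = 0.409. With 405 per arm it is 0.403. With 100 per arm it is 0.46.

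**4. Chance that an arm is above 6% at 7 years, both on plan.** 6% of 385 is 23.1, so 24 events are needed. Because 23.1 is not a whole number, *above* and *at or above* give the same count. P(X ≥ 24 | 385, 0.06) = 0.453 per arm. For at least one arm: 1 − (1 − 0.453)² = 0.701. With 405 per arm it is 0.720.

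**5. Chance that both conditions are met** (some arm above 5% at 5 years and some arm above 6% at 7 years):

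| Weibull shape | 5-year rate | Look | Above 6% at 7 years | Both |
|---|---|---|---|---|
| 0.5 | 5.10% | 0.75 | 0.70 | 0.66 |
| 0.75 | 4.69% | 0.58 | 0.70 | 0.55 |
| 1.0 | 4.32% | 0.41 | 0.70 | 0.40 |
| 1.25 | 3.98% | 0.26 | 0.70 | 0.26 |

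These rows use 385 per arm. Taking 405 per arm as well, the last column spans 0.25 to 0.67.

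**6. Conflict with the margin.** With RT observed at 6% and the planning variance, the largest observed difference that still meets the margin is 5 − 1.645 × √(2 × 0.06 × 0.94 / 385) × 100 = 5 − 2.8 = 2.2 points, a tamoxifen rate of about 8.2%. Using the observed tamoxifen rate in the variance brings this to about 2.0 points. Either way, such a trial would show non-inferiority with both arms at or above the discontinuation level. If tamoxifen is truly 8% at 7 years (5.78% at 5 years), its arm exceeds the 5-year trigger with probability 0.72 and 6% at 7 years with probability 0.92.

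**The case against.** A reader might infer that the design itself expects 5% at 5 years and that a trial on plan would therefore probably be stopped. The document does not support this. It states no 5-year expectation, and its 7-year assumption implies about 4.3%; only a strongly front-loaded hazard brings 5%. Exceeding 5% opens an analysis, so the probabilities in step 3 are chances of a look. Whether stopping is more likely than not depends on how an unclear sentence is read: about 70% on one reading, about 40% on another.

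Other points on that side also have weight:

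- The 70% assumes complete 7-year data in full arms. That is close to the dataset for the final comparison, so by then little may be left to stop. No probability of stopping on immature data has been derived.
- It would be loose to say that the design accepts tamoxifen up to 11%. With RT at 6%, that is the null boundary; step 6 shows how much lower the observed rate must be.
- No early claim of non-inferiority is described, so inflation of type I error or distortion of the final inference is not shown.
- An absolute ceiling is a recognisable safeguard when standard treatment is omitted.
- The article condenses a fuller protocol (version 2.0), and a monitoring committee has access to the data. Boundary details may well be there.

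These points limit the size and wording of the finding. They do not remove it. The article prints a discontinuation level, and that level equals its own planning rate. This is a conflict between two stated figures, and a fuller document would have to change the printed rule to resolve it.

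**Conclusion.** The point holds in this form: the discontinuation level coincides with the planned rate in both arms, the look opens about 0.7 points above the implied 5-year rate, and neither refers to the between-arm difference. If the rule means stopping when an arm reaches 6%, a trial exactly on plan meets it with probability about 70% when the 7-year level stands alone. If the 5-year trigger must come first, the probability is about 40% (25% to 67% by hazard shape). Both figures assume independent arms, complete follow-up and one look; repeated looks or fewer patients at risk would change them. Even the lower figure is high for a trial with nothing wrong, and a discontinuation rule that can be read two ways is a defect in itself.

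**What to change.** Reconcile the Interim analyses section with the Sample size section and Table 2:

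- Remove the absolute per-arm levels as grounds for discontinuing the trial.
- In their place, prespecify a comparison of IBTR between arms (tamoxifen minus RT) in all randomized patients, at a fixed information point, with a stringent boundary for harm only. The sponsor and its monitoring committee should choose the information point and the boundary.
- If an absolute level is kept, state its direction and time point and let it prompt committee review only.

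The cost is an amendment, one committee report and a small loss of power, which should be computed for the boundary chosen. The change is cheap now: the Trial status section reports 36 patients enrolled by December 2022, and with first enrolment in July 2019 no patient could reach 5 years before July 2024.

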### Adverse event reporting and harms

The assessment of acute toxicities (≤ 90 days from the start of RT) and adverse effects of tamoxifen will be scored using the Common Terminology Criteria for Adverse Events (CTCAE), version 4.03 [32]. We will score late RT toxicities (> 90 days from the start of treatment) using the RTOG/European Organization for Research and Treatment of Cancer Late Radiation Morbidity Scheme [33].

We will record serious adverse events (SAEs), which must fulfill at least one of the following criteria: (1) an unexpected event that immediately results in risk of death; (2) the events require patients to be hospitalized for further care or prolong hospitalization; and (3) the events cause significant or persistent incapacity or disability.

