**Methods/design:**

This is a prospective, international, open-label, randomized, non-inferiority trial. Patients with low-risk clinicopathologic features (> 40 years old, low risk of breast cancer susceptibility gene (*BRCA) 1* and *BRCA2* mutations, mammographically detected unicentric and non-mass lesions, low- or intermediate-grade without comedo or necrosis, measuring < 2.5 cm with margins ≥ 3 mm, and estrogen receptor-positive status) of DCIS who underwent BCS will be randomized at a 1:1 ratio to either receive tamoxifen (5 mg/day) for 5 years or undergo RT with conventional fractions (50 Gy in 25 fractions) or hypofractionations (40.05 Gy in 15 fractions). Randomization will be stratified by the Taiwan Breast Cancer Consortium. As approximately 5% of patients cannot tolerate the side effects of low-dose tamoxifen and will receive RT, we estimate that 405 patients will be randomized to a low-dose tamoxifen arm and 405 patients to the RT arm, according to a non-inferiority margin within 5% of IBTR difference and 90% β-power noticing non-inferiority. The primary endpoints are breast tumor recurrence, including ipsilateral, regional, contralateral, and distant recurrence of breast DCIS or invasive cancer. The secondary endpoints are overall survival and adverse effects of RT and tamoxifen. Translational studies will also be conducted for this trial.

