### Interventions

#### Intervention description

In the current study, patients who are randomized to the RT arm will undergo RT with 50 Gy divided in 25 fractions (2 Gy each) or with 40.05 Gy divided in 15 fractions (2.67 Gy each); RT dose and fractions will be dependent on the institution’s experience. RT for treating the whole breast will be delivered daily from Monday to Friday; however, regional lymphatic irradiation and boost of the tumor bed will not be allowed.

All patients randomized to the tamoxifen treatment arm will receive tamoxifen (5 mg/day) for 5 years. Tamoxifen toxicities, including hot flashes, transient nausea, and vaginal discharge, are minimal, whereas skin rash, vaginal bleeding, edema, and embolisms seldom occur. As the drug compliance of patients who are randomized to low-dose tamoxifen is crucial, the adherence to taking 5 mg tamoxifen was defined as the use of at least 90% of these pills each year for at least 5 years.

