### Outcomes

Our primary objective is to observe breast tumor recurrence, including ipsilateral, regional, contralateral, and distant recurrences of breast cancer (DCIS or invasive cancer events).

Our secondary objective is to assess overall survival in all patients, adverse effects of RT and tamoxifen, and translational studies—including single nucleotide polymorphisms (SNPs), extracellular matrix (ECM)- and immune-related molecules, and mutational analyses of selected genes.

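### After day 90 toxicity is graded by treatment on two different scales, so late non-serious adverse effects cannot be compared between the arms like with like

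*Protocol article*

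**What the plan says.** - **Endpoint.** The abstract states: "The secondary endpoints are overall survival and adverse effects of RT and tamoxifen". The Outcomes section agrees: "Our secondary objective is to assess overall survival in all patients, adverse effects of RT and tamoxifen, and translational studies". Neither names a between-arm contrast, a grade threshold or a test.
- **Scale up to day 90, and for tamoxifen.** Adverse event reporting and harms names CTCAE v4.03 here: "The assessment of acute toxicities (≤ 90 days from the start of RT) and adverse effects of tamoxifen will be scored using the Common Terminology". The 90-day limit belongs to acute toxicity. Tamoxifen effects carry no time limit.
- **Scale after day 90 for RT.** The same section turns to a scale made for late radiation effects: "We will score late RT toxicities (> 90 days from the start of treatment) using the RTOG/European Organization for Research and Treatment of Cancer".
- **What is recorded.** The Participant timeline section describes the adverse events entered on the case report form as those caused by RT or by low-dose tamoxifen.
- **When.** Table 1 has one adverse-event row for both arms, from 0–3 months to year 10. The section on plans for assessment and collection of outcomes places RT toxicity during or after RT, and tamoxifen toxicity once the tamoxifen course has ended.
- **Serious events.** "We will record serious adverse events (SAEs), which must fulfill at least one of the following criteria". The list that follows is tied to neither arm nor scale.
- **Expected tamoxifen effects.** Intervention description: "Tamoxifen toxicities, including hot flashes, transient nausea, and vaginal discharge, are minimal, whereas skin rash, vaginal bleeding, edema, and embolisms seldom occur".

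**The concern.** A randomized trial's strength for harms is that the control arm supplies the background rate. That needs the same events to be sought and graded in the same way in both arms, whatever the investigator thinks caused them. Here both the grading rule and the recording sentence are organized by presumed cause. The trial is open-label, so the person judging cause knows the treatment.

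Two things are at stake. First, a late skin or breast event attributed to RT is graded on one instrument and one attributed to tamoxifen on another, and a grade on one is not a grade on the other. Second, vasomotor and gynecologic events in the tamoxifen arm would be reported without a matching graded rate from the RT arm. The part of that rate that would have occurred without the drug could then not be subtracted.

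This bears on how the result would be used. The Discussion offers low-dose tamoxifen as an alternative for patients who wish to avoid RT on account of its possible side effects. Advising such a patient requires relative toxicity, most of it non-serious and late.

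**Working it through.** No arithmetic decides this point, and the plan states no figure to reproduce. The check sets the sections side by side.

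**Step 1. Which scale applies to which event, as written.**

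| Event | Up to day 90 | After day 90 |
|---|---|---|
| Effect attributed to tamoxifen | CTCAE v4.03 | CTCAE v4.03 |
| Effect attributed to RT | CTCAE v4.03 | RTOG/EORTC late scheme |
| Non-serious event in an RT patient, not attributed to RT | CTCAE v4.03 if counted as acute toxicity | No scale stated |
| Serious adverse event, either arm | One common definition | One common definition |

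The right-hand column shows both faults: two instruments in the first two rows and no stated instrument in the third.

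**Step 2. How much of the trial falls in the right-hand column.** Tamoxifen is given for 5 years and Table 1 collects adverse events to year 10. Most tamoxifen exposure therefore comes after day 90. This describes time only. It does not measure lost information, because events need not be spread evenly.

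**Step 3. Does Table 1 close the gap?** Only in part. Its single row fixes visit times for both arms. It does not say which events count or on what scale. The Participant timeline section, which introduces the table, words the events by cause.

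**Step 4. Do serious adverse events close the gap?** They give a valid comparison over the whole follow-up, but for a small part of the burden. The article's Background cites 12 of 249 patients with serious events on low-dose tamoxifen in the earlier randomized trial: 12/249 = 4.8%. Hot flashes and vaginal discharge, which the Intervention description lists as tamoxifen toxicities, would seldom meet the seriousness criteria.

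**Step 5. Timing.** Table 1 records adverse events from 0–3 months. The outcome-collection section puts assessment of tamoxifen toxicity after the 5-year course has ended. Both cannot describe the same data collection.

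**Step 6. Is it too late to change?** Trial status reports 36 patients enrolled by December 2022, out of 810 planned. That leaves 810 − 36 = 774 patients, or 774/810 = 95.6% of the target, who could be followed under a corrected rule from the start, counting from that date.

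**The case against.** The strongest reply has four parts.

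1. **Missing detail is not a fault.** A journal article condenses the full protocol, and grading instructions are usually found elsewhere. That would answer a complaint about silence alone. It does not answer this one, because the article states a rule, and the rule is specific to treatment and based on attribution.
2. **Each scale suits its purpose.** A late radiation scale is apt for describing late radiation effects, and the endpoint wording fits a separate description of each treatment. This stands as a reason to keep the scheme. It does not justify giving up the randomized control for harms in a two-arm trial.
3. **Comparison is not impossible.** A reader might infer that the adverse-effects endpoint cannot be compared between arms at all. The documents do not support that. Serious events share one definition, toxicity up to day 90 shares CTCAE, and the shared visit schedule allows some comparison of raw occurrence.
4. **RT-arm events are not said to be ignored.** A reader might infer that after day 90 RT patients are scored for late radiation effects and nothing else. The text assigns the late scheme to a kind of toxicity. It does not exclude other events from recording or from CTCAE grading. The supportable statement is that no grading is stated for them.

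One further inference should be avoided. The Discussion's remark on fewer side effects rests on the earlier trial of low-dose tamoxifen against observation. It is not a claim that tamoxifen is less toxic than RT.

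**Conclusion.** The point holds in limited form. After day 90, treatment-attributed grades come from two instruments, and no common, all-cause grading of non-serious events is stated for both arms. Late non-serious toxicity therefore cannot be compared like with like, and the tamoxifen rates lack a randomized control rate. Serious events and toxicity up to day 90 are not affected in this way.

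The size cannot be quantified, because the documents give no background rates for vasomotor or gynecologic events in this population. The conclusion assumes that the full protocol follows the rule printed in the article, and that some of these events would also occur in women not taking tamoxifen. The primary endpoint and the sample size are untouched. This is an inexpensive improvement to a secondary endpoint, not a flaw that endangers the trial.

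**What to change.** - Record and grade all adverse events with CTCAE v4.03 in both arms, regardless of suspected cause, at every adverse-event visit already in Table 1. Amend the attribution wording in the Participant timeline section to match.
- Name this common grading as the basis of the between-arm safety comparison.
- Keep the RTOG/EORTC late scheme as an additional, RT-specific measure.
- Reconcile the outcome-collection section, which places tamoxifen toxicity assessment after the course ends, with Table 1, which starts at 0–3 months.

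The cost is a short protocol amendment and slightly more data entry for RT patients at visits that already exist. For patients already enrolled, the report should say from what date the common grading applies.

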## Discussion

We previously demonstrated that among patients who did not receive RT in our institution (National Taiwan University Hospital [NTUH] cohort), ER-negative status was significantly correlated with a higher IBTR rate [7]. We also collected the clinicopathological features of 1,964 patients from 12 Taiwan hospitals (Taiwan cohort) and assessed the relationship between ER status and IBTR in breast DCIS patients who underwent BCS [34]. We found that in patients who did not receive RT, those with ER-negative DCIS had a higher 7-year IBTR than those with ER-positive DCIS (23.9% vs. 5.4%, *P* = 0.007) [34]. The results of the NTUH and Taiwan cohorts demonstrated that among patients with breast DCIS who underwent BCS alone, ER-negative status in tumors was closely associated with a higher IBTR. Our results are consistent with previous reports showing that patients with ER-negative tumors had a higher incidence of local recurrence than those with ER-positive tumors after undergoing BCS without RT [10, 35, 36].

In addition to ER-negative status in tumors, we previously reported that age < 40 years was significantly associated with the risk of IBTR in breast DCIS patients who underwent BCS alone [7]. Cronin et al. also demonstrated that age < 40 years was a prognostic factor for local recurrence in patients with breast DCIS who underwent BCS with and without RT [11]. Tunan-de-Lara et al. also reported that age ≤ 40 years was independently associated with higher local recurrence of breast DCIS regardless of the pathological features of the tumor [12].

For patients with low-risk DCIS who underwent BCS alone in the ECOG E5194 and RTOG 9804 trials [4–6], the risk for DCIS and invasive cancer increased slightly, indicating that RT is needed for this subtype of breast DCIS. However, a proportion of patients who were aged < 40 years and those who had ER-negative tumors—who were at risk of IBTR if they underwent BCS without RT—were enrolled [4–6]. Because tamoxifen has demonstrated higher clinical efficacy in reducing local recurrence in ER-positive than in ER-negative DCIS [9], it is reasonable to hypothesize that the efficacy of low-dose tamoxifen in decreasing local recurrence is not inferior to RT in patients aged > 40 years with low-risk (cohort 1 characteristics of the ECOG E5194 trial) and ER-positive breast DCIS.

Nevertheless, tamoxifen has an estrogenic effect on the endometrium and has been reported to increase the risk of endometrial cancer; tamoxifen-associated endometrial cancers are a localized disease with rare morbidity [37, 38]. Previous studies also demonstrated that the administration of low-dose tamoxifen (1–5 mg/day) had biological effects on breast cancer in terms of the Ki-67 index and lower endometrial cell proliferation [39, 40]. In a single institute experience with tamoxifen in the adjuvant setting for patients with breast DCIS, Guerrieri-Gonzaga et al. found that low-dose tamoxifen (5 mg per day) reduced ipsilateral recurrence in women aged > 50 years with ER-positive DCIS [41]. In a median follow-up of 9.7 years of a randomized trial of TAM-01, the 3-year administration of low-dose tamoxifen (5 mg for 3 years) resulted in a significant decline of 50% recurrence in the patients with DCIS without increased adverse effects [42]. Considering that low-dose tamoxifen significantly decreased local recurrence and caused fewer side effects in patients with breast DCIS from the data of a randomized trial (TAM-01) [13, 42], we theorized that low-dose tamoxifen is similar to standard-dose tamoxifen in terms of preventing recurrence in low-risk DCIS patients.

In conclusion, this prospective study aims to evaluate whether low-dose tamoxifen administration is not inferior to RT in decreasing local recurrence in women aged > 40 years with low-risk characteristics and ER-positive breast DCIS who have undergone BCS. If this study confirms its primary endpoint, it will provide an important alternative for clinical physicians to recommend adjuvant low-dose tamoxifen for patients with low-risk breast DCIS who do not want to receive adjuvant RT because of potential side effects. Moreover, the cost of low-dose tamoxifen is lower than that of RT. We believe that this non-inferior trial will be helpful in prospective clinical practice in patients with specific low-risk breast DCIS.

